## D. Personalized training progression

Physiotherapists will personalize the training progression according to the participants' level of exertion. This personalization of the training progression will be recorded. A record will be kept regarding V1, V2 and V3, total duration of walking, and duration of rests at each session. In personalizing the participant's progression, the guidelines below will be followed.

### *Personalized progression of speed*

Speeds are only increased by 5% at V2 and V3 if the previous maximum attained speed was tolerated. If after starting any walking training trial (V1/V2/V3) the speed is not tolerated, the speed will be lowered 5% to the previously tolerated walking speed before the bout is resumed.

### *Personalized progression of duration*

If the participant tolerates the speed but not the duration of the walking training period, the duration of V2 and V3 will be shortened (-30 seconds) to the previously tolerated walking duration during the training trials. In addition, they are given a longer recovery walking period at 70% CS (+30 seconds) and on top of this a seated resting break can be included if needed.

### *Personalized progression of VR*

An automatic progress mode in the system allows VR progression to be personalized, based on the subjects performance.

## ix. Post-Training (T1)

After each *training phase*, participants in all groups across all centers will undergo another *functional assessment*, including measurement of clinical outcomes and a gait analysis during which EEG, EMG and kinematics data will be collected. As done at To a video of the participants head will be taken to determine the electrode position.

## A. Functional assessment

### *Clinical assessments*

We will assess changes in functional mobility with the standard timed-up-and-go (TUG) test and the 2-minute walk test, balance and fall risk with the MiniBESTest, and motor symptoms of PD with the MDS-UPDRS. We will use questionnaires to assess effects on gait self-efficacy (modified gait efficacy scale, mGES and falls efficacy scale international, FES-i), fatigue (FACIT-F) and health-related quality of life (EQ-5D).

### *Kinematic and neurophysiological measures*

We will assess preferred gait speed and maximal gait speed using a 20-m walk test (Primary outcome).

Participants start walking on the treadmill for 7 minutes for familiarization. After that, they will then walk at their preferred speed for 5 minutes, to assess the secondary outcomes, step-width and stride-time and the variance of these parameters, from data of at least 100 strides. The fixed 1.4 km/h is attainable for an estimated 95% of patients with moderate PD. However, for those who cannot attain 1.4 km/h at To, their preferred walking speed To will be their fixed speed during all functional assessments. The treadmill assessment will be repeated at their preferred speed. Additionally, during Treadmill walking data from the EEG and EMG will be collected to derive beta-band power in motor areas and calculate cortico-muscular coherence (CMC) between brain and muscle activity.

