#### *Kinematic and neurophysiological measures*

We will assess preferred gait speed using a 20-m walk test (Primary outcome).

Participants start walking on the treadmill for 7 minutes for familiarization. After that, they will then walk at a fixed speed of 1.4 km/h for 5 minutes, to assess the secondary outcomes, step-width and stride-time and the variance of these parameters, from data of at least 100 strides. The fixed 1.4 km/h is attainable for an estimated 95% of patients with moderate PD. However, for those who cannot attain 1.4 km/h at To, their preferred walking speed To will be their fixed speed during all functional assessments. The treadmill assessment will be repeated at their preferred speed. Additionally, during Treadmill walking data from the EEG and EMG will be collected to derive beta-band power in motor areas and calculate cortico-muscular coherence (CMC) between brain and muscle activity.

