### *Kinematic and neurophysiological measures*

We will assess preferred gait speed and maximal gait speed using a 20-m walk test (Primary outcome).

Participants start walking on the treadmill for 7 minutes for familiarization. After that, they will then walk at their preferred speed for 5 minutes, to assess the secondary outcomes, step-width and stride-time and the variance of these parameters, from data of at least 100 strides. The fixed 1.4 km/h is attainable for an estimated 95% of patients with moderate PD. However, for those who cannot attain 1.4 km/h at T0, their preferred walking speed T0 will be their fixed speed during all functional assessments. The treadmill assessment will be repeated at their preferred speed. Additionally, during Treadmill walking data from the EEG and EMG will be collected to derive beta-band power in motor areas and calculate cortico-muscular coherence (CMC) between brain and muscle activity.

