**Dependent variables:**

*primary clinical outcomes:*

- preferred gait speed (20 m walk test)
- stride length (at preferred speed)
- stride length (at 1.4 km/h)

*secondary clinical outcomes (T1):*

- stride length variability (at preferred speed and at 1.4 km/h)
- stride time (at preferred speed and at 1.4 km/h)
- stride time variability (at preferred speed and at 1.4 km/h)
- step width (at preferred speed and at 1.4 km/h)
- step width variability (at preferred speed and at 1.4 km/h)
- falls
- timed-up-and-go (TUG) test
- 2-minute walk test
- MiniBESTest
- MOCA
- MDS-UPDRS, part III
- mGES

*secondary clinical outcomes (T2):*

- steps per day
- uninterrupted walk durations
- stride time variability
- symmetry

*feedback control variables (T1 all at 1.4 km/h):*

- $R^2$  (feedback model relating foot placement to centre of mass movement)
- RMS error (feedback model relating foot placement to centre of mass movement)
- Position gain (feedback model relating foot placement to centre of mass movement)
- Velocity gain (feedback model relating foot placement to centre of mass movement)

*neural correlates (T1 all at 1.4 km/h):*

- EEG beta power in(pre-)motor areas during walking at preferred speed
- EEG-EMG coherence during walking at preferred speed

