### **Independent variables:**

*feedback control variables (T1-To / T2-To, at 1.4 km/h):*

- $\Delta R^2$  (feedback model relating foot placement to centre of mass movement)
- $\Delta$  RMS error (feedback model relating foot placement to centre of mass movement)
- $\Delta$  Position gain (feedback model relating foot placement to centre of mass movement)
- $\Delta$  Velocity gain (feedback model relating foot placement to centre of mass movement)

*neural correlates (T1-To / T2-To, at 1.4 km/h):*

- $\Delta$  beta power during walking at preferred speed
- $\Delta$  EEG-EMG coherence during walking at preferred speed

Associations between feedback control variables and neurological correlates

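### The T1 and T2 treadmill instructions omit the fixed 1.4 km/h walk that section 6 needs after baseline, and the neural outcomes are assigned to two speeds at once

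*Protocol*

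**What the plan says.** **Procedures.** Protocol section 5.vii.A (T0) has a 7-minute familiarization, after which "they will then walk at a fixed speed of 1.4 km/h for 5 minutes". It then adds "The treadmill assessment will be repeated at their preferred speed". Patients who cannot reach 1.4 km/h get a fallback: "their preferred walking speed To will be their fixed speed during all functional assessments".

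Section 5.ix.A (T1) changes the first walk: "they will then walk at their preferred speed for 5 minutes, to assess the secondary outcomes, step-width and stride-time". Section 5.xi.A (T2) does the same: "they will then walk at their preferred speed for 5 minutes". Both keep the T0 sentence on the repeat at preferred speed, the remark on how many patients can attain the fixed 1.4 km/h, and the fallback rule for those who cannot.

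**Analyses.** Section 6.vi (2a) and section 6.vii (3a) list stride length at 1.4 km/h among the primary clinical outcomes and give five secondary gait measures at both speeds. They head the foot-placement variables "feedback control variables (T1 all at 1.4 km/h". Section 6.viii (3b) uses T1-T0 and T2-T0 changes in those foot-placement variables at 1.4 km/h, both as predictors and as outcomes.

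**Neural outcomes.** In 3b the heading is "neural correlates (T1-To / T2-To, at 1.4 km/h", while the item beneath it is "beta power during walking at preferred speed". EEG-EMG coherence carries the same pair of speeds. The conflict recurs in every list that defines these outcomes (1a, 1b, 2a, 3a and 3b).

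**The concern.** Section 6.ii states that the main aim is mechanism. Analysis 3b serves it by relating changes in gait to changes in foot-placement control and in neural measures. A fixed treadmill speed holds walking speed constant across visits, so that a change in foot placement or cortical activity is not simply the result of walking faster. If the fixed-speed walk is not recorded at T1 and T2, that comparison is lost and cannot be recovered later.

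Four centres work from this text. One may infer the fixed walk and another may follow the literal instruction, so missing data would depend on centre. Perturbation type also depends on centre (Table 2).

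For the neural outcomes, two speeds under one label leave the choice to the analyst after the data have been seen.

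**Working it through.** No figure stated in the plan is at issue. The check is a comparison of text, plus one unit conversion.

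**1. Treadmill walks instructed at each visit**

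| Visit | Section | First 5-minute walk | Repeat | Fixed-speed sentences present? |
|---|---|---|---|---|
| T0 | 5.vii.A | fixed 1.4 km/h | preferred | yes |
| T1 | 5.ix.A | preferred | preferred | yes |
| T2 | 5.xi.A | preferred | preferred | yes |

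At T1 and T2 preferred speed is instructed twice and 1.4 km/h not at all. Each of these paragraphs also contradicts itself. The fallback rule presupposes a fixed-speed walk at every functional assessment, and a repeat at preferred speed makes sense only if the first walk was at some other speed.

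**2. What section 6 needs at 1.4 km/h after baseline**

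| Variables | 2a and 3a | 3b |
|---|---|---|
| Stride length | listed as primary; 3a models T0, T1 and T2 | T1-T0 and T2-T0 |
| Stride length variability, stride time, stride time variability, step width, step width variability | T1 | T1-T0 and T2-T0 |
| R-squared, RMS error, position gain, velocity gain | T1 only | T1-T0 and T2-T0 |

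The clinical dependent variables in 3b also include preferred-speed versions and the 20-m walk. In 3c the feedback variables carry no speed. T2 foot-placement values at 1.4 km/h are therefore needed only in 3b. Analyses 1a and 1b use pre-training data, so the missing walk does not touch them; they share only the neural labelling conflict.

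**3. Can preferred-speed values substitute?**

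Inputs: the fixed speed of 1.4 km/h (5.vii.A) and the quoted baseline overground speed of 1.26 m/s (6.i).

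- Fixed speed: 1.4 / 3.6 = 0.389 m/s
- Baseline: 1.26 × 3.6 = 4.54 km/h
- Ratio: 1.26 / 0.389 = 3.24; conversely 0.389 / 1.26 = 0.31

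The fixed speed is about 31% of the quoted overground baseline. Preferred treadmill speed is not given and may be lower than overground speed, so this shows scale only. Even so, the two conditions are not interchangeable, and subtracting a 1.4 km/h baseline from a preferred-speed follow-up would mix a change in condition with a change in the patient.

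**4. Neural outcomes**

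In 1a, 1b, 2a, 3a and 3b the heading gives 1.4 km/h and both items give preferred speed. The two cannot both define the same variable.

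**The case against.** The strongest reply is that the intent is already clear. The fallback rule at T0 covers all functional assessments, T1 and T2 repeat it, and T1 and T2 are introduced as further instances of the same assessment. On that view one phrase was altered in a copied paragraph, and no condition was dropped. Much of this stands: a drafting slip is the likelier explanation. But the sentence that tells staff which walk to run says preferred speed, at both post-baseline visits, and a later analysis plan cannot repair a walk that was not recorded.

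A reader might go further than the documents allow in four ways.

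- **All post-baseline 1.4 km/h data will be missing.** That holds only if sites follow the literal instruction. It is a consequence of the wording and not a forecast.
- **The primary endpoint is compromised.** It is not. Sections 4.iii and 6.i rest on gait speed, and section 5.xii (C1) takes it from the overground 20-m walk. Stride length at 1.4 km/h is called primary only in the section 6 lists.
- **Section 6.i gives the expected rise in walking speed, and so the size of any confounding.** The 0.1 and 0.08 m/s quoted there are upper figures for contrasts between types of training, measured overground. They are not expected within-patient changes, and the protocol gives none.
- **No valid treadmill comparison remains.** T0 also records a preferred-speed walk, so like-for-like comparisons at preferred speed stay available. They do not replace the fixed-speed variables that 2a, 3a and 3b name.

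For the neural outcomes, the documents show only that heading and items conflict. They do not show which speed was meant.

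**Conclusion.** The point holds as an internal contradiction with consequences for the main aim. Read literally, sections 5.ix.A and 5.xi.A leave these without post-baseline values: stride length at 1.4 km/h, the five fixed-speed secondary gait measures, and the four feedback-control variables (T1 in 2a and 3a; T1-T0 and T2-T0 in 3b). The preferred-speed walk cannot supply them. The gait-speed primary endpoint and the sample size are unaffected.

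The size of any actual loss depends on what the sites do, which the protocol does not settle. The two-speed labelling of beta power and EEG-EMG coherence is a separate contradiction, present in all five lists that define them. Both should be corrected before further T1 and T2 visits take place.

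**What to change.** **Treadmill walks.** In sections 5.ix.A and 5.xi.A, restore the sequence of section 5.vii.A: 5 minutes at the fixed 1.4 km/h, or at the patient's own fixed speed set at T0, and then the repeat at preferred speed. Two walks are already scheduled at each visit, so no visit time is added. Tell all four centres, and establish which speed was used at any T1 or T2 visit already completed.

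**Neural outcomes.** In 1a, 1b, 2a, 3a and 3b, make heading and items agree, so that beta power and EEG-EMG coherence each have one stated main speed. Fixed speed has the advantage for the mechanism analyses that neural change is not mixed with change in walking speed. That is a recommendation, since the documents support either label. The other speed can be reported as a sensitivity analysis.

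The cost is a text amendment and a notice to the sites.

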## **B. Home assessment**

A home assessment visit for the period of at least 7 days should be completed. Participants will wear inertial measurement units (IMUs), either a single unit on the lower back or, in a subgroup, a three-sensor system, to continuously record motion data. The sensor on the lower back will be attached using medical tape, while the ankle sensors will be fastened using a self-adjustable band to ensure participant comfort. The sensors can be removed quickly and can be easily repositioned following the instructions provided. The planned number of participants to wear the 3-sensor setup at each site for each interventions follows:

- i. 20 people from SDTT (5 each from Sydney, Kiel, Bologna and Tel Aviv)
- ii. 16 people from SDTT + VR (8 each from Bologna and Tel Aviv)
- iii. 8 people from SDTT + MP (Kiel)
- iv. 8 people from SDTT + VR + MP (Sydney)

Participants will be chosen in order of participation until the minimum sample size required is reached.

Participants will be asked to complete a daily diary via their personal smartphone or by paper pencil depending on their preference, including the following information: medication intake, physical activities performed, freezing of gait (FOG) episodes, falls experienced and information on fatigue. Other than the clinical assessment, that is performed during ON medication, the home assessment contains periods of ON, OFF, and transitions between phases, along with various contextual factors that influence mobility. To accurately evaluate the relationship between improvements in lab-based and daily-life gait outcomes, this diary records the influence of Parkinson's medication and physical activity on mobility during the home assessment and ensures with that comparability between the gait outcomes of To and T1. During the functional assessment, participants receive support in personalizing the diary by entering their medication schedule and adding typical physical activities. Over seven days, the diary is completed daily and is expected to take 1–3 minutes per day. Only deviations from the medication schedule need to be noted, while normal intake can simply be checked off for each day. Physical activities, FOG episodes, and falls can be logged by adding abbreviations/X marks in the provided timetable. Participants are encouraged to keep the diary beside their medication box to help prevent late entries, while no daily reminders will be sent to minimize the burden on participants.

## **C. Qualitative interviews**

Online questionnaires will be used to assess:

- System usability
- Physical Activity Enjoyment
- Exercise Self Efficacy
- Barriers and Enablers to long term use

Furthermore, space for participants to provide feedback and suggestions for future improvements will be used to record all participants' experiences of the treadmill training.

### **x. Maintenance Period (T1 to T2)**

#### **A. Home-based walking**

All participants will be offered a home-based speed dependent walk training intervention. This intervention is an App based training for gait adaptability and allows users to set their own training time and pace. It delivers a rhythmic metronomic beat for three different walking speeds, designed to trigger movement and encourage better walking patterns. The Walking Tall app can be installed on iOS and Android devices and does not store any personalized data. During the maintenance period, participants will be supported using the app to progress towards World Health Organisation recommendations for moderate intensity exercise through a personalised goal setting session.

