| Intervention                       | Speed-dependent treadmill training (i.e, treadmill walking at alternating blocks of different percentages of comfortable walking speed) for 12 sessions with perturbations (sessions between T0 and T1).                                                                                                                  |                  |
| Control                            | Speed-dependent treadmill training without perturbations (12 sessions between T0 and T1).                                                                                                                                                                                                                                 |                  |
| Maintenance                        | Both groups receive home-based speed-dependent walk training using a phone app for maintenance of treadmill training benefits between the T1 post-training and T2 follow-up assessments. Includes goal setting towards World Health Organisation physical activity recommendations.                                       |                  |
| Outcomes                           | Measures                                                                                                                                                                                                                                                                                                           | Domain    |
|                                    | Primary outcome
Gait speed (m/sec)                                                                                                                                                                                                                                                                                     | Gait performance |
|                                    | Step width
Step width variability
Stride time
Stride time variability
Stride length variability
Stride length                                                                                                                                                                                              | Walking          |

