### ii. Objectives

Thus, the **objectives** of our StepuP project are:

1. To understand the kinematic and neural mechanisms that underlie improvements in gait due to treadmill training with and without mechanically and VR-triggered gait adaptations in people with PD;
2. To assess to what extent improvements in gait due to treadmill training, as measured in the lab, transfer to improvements in daily life mobility;
3. To understand the mechanisms that underpin transfer from improvements in gait to improvements of mobility in daily life in people with PD;
4. To understand for whom treadmill training improves lab-based gait characteristics and for whom it does not, and understand for whom treadmill training improves mobility in daily life and for whom it does not.

Attaining these objectives will provide a better understanding of the successes and failures of treadmill training to improve gait stability and prevent falls in people with PD at an individual level, which in the medium term will allow targeted delivery of such interventions and in the long term will allow personalization of such interventions to improve outcomes for all.

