##### **Post-Training**

The Post-Training phase including *home assessment and functional assessment (T1)* will last for a total of 14 days. There should not be more than 2 days between second functional assessment and the end of the last training visit. Also, the home-assessment should not start later than 5 days after the second functional assessment.

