**Dependent variables:**

*primary clinical outcomes:*

- preferred gait speed (20 m walk test)
- stride length (at preferred speed)
- stride length (at 1.4 km/h)

*secondary clinical outcomes (T1):*

- stride length variability (at preferred speed and at 1.4 km/h)
- stride time (at preferred speed and at 1.4 km/h)
- stride time variability (at preferred speed and at 1.4 km/h)
- step width (at preferred speed and at 1.4 km/h)
- step width variability (at preferred speed and at 1.4 km/h)
- falls (diary)
- timed-up-and-go (TUG) test
- 2-minute walk test
- MiniBESTest
- MOCA
- MDS-UPDRS, part III
- mGES

*secondary clinical outcomes (T2):*

- steps per day
- uninterrupted walk durations
- stride time variability
- symmetry

*feedback control variables (T1 all at 1.4 km/h):*

- $R^2$  (feedback model relating foot placement to centre of mass movement)
- RMS error (feedback model relating foot placement to centre of mass movement)
- Position gain (feedback model relating foot placement to centre of mass movement)
- Velocity gain (feedback model relating foot placement to centre of mass movement)

*neural correlates (T1 all at 1.4 km/h):*

- EEG beta power in(pre-)motor areas during walking at preferred speed
- EEG-EMG coherence during walking at preferred speed

Linear mixed effect models with the interaction of treatment and time in the model and a random intercept for participant nested within center (Twisk et al., 2018), controlling for relevant potential confounders (e.g., age, H&Y stage). For the EEG data, we will use cluster-based permutation tests time locked to the gait cycle.TT)

vii. Independent RCTs SDTT vs SDTT+ (3a)

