### **Analysis technique:**

We will correlate changes in primary outcomes (e.g., walking speed) with changes in behavioural (foot placement coordination) and neural (EEG beta band power, cortico-muscular coherence) outcomes. Multilevel models will be used, to account for data collected at different sites. For outcomes T2-To, potential predictors of clinical outcomes will include independent variables with a time lag (T1-To) and without time lag (T2-To).

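### The protocol does not say whether the T1 home-recording week precedes the walking app, and it lists the randomised daily-life comparison only at T2, after the app period

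*Protocol*

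**What the plan says.** Protocol section 5.x.A (Home-based walking) states: "All participants will be offered a home-based speed dependent walk training intervention". The app sets walking rhythms at three speeds, and in the same period "participants will be supported using the app to progress towards World Health Organisation recommendations for moderate intensity exercise through a personalised goal setting session". The Trial Summary gives the window as "for maintenance of treadmill training benefits between the T1 post-training and T2 follow-up assessments" and says both groups receive it. Neither place gives a start day.

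The T1 home recording belongs to the 14-day Post-Training phase (section 5.iv). The T1 functional assessment takes place within 2 days of the last training session, and "the home-assessment should not start later than 5 days after the second functional assessment". Section 5.ix.B asks for at least 7 days of recording. T2 follows 12 weeks (plus or minus 2) after the Post-Training phase ends.

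The second objective (section 4.ii) is: "To assess to what extent improvements in gait due to treadmill training, as measured in the lab, transfer to improvements in daily life mobility". Section 6.ix tests this with T1-minus-T0 changes in steps per day, uninterrupted walk durations, stride time variability and symmetry, regressed on T1-minus-T0 laboratory changes, with a mediation analysis for gait efficacy (mGES). The randomised comparisons 2a and 3a (sections 6.vi and 6.vii) place these four daily-life outcomes under a heading that begins "secondary clinical outcomes (T2" and under no other. The mechanism analysis 3b (section 6.viii) models both T1-minus-T0 and T2-minus-T0 change. Section 6.x names retention among the things to be understood.

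**The concern.** The app programme acts directly on what the home sensors measure. Goal setting aims at more walking, which is steps per day and walk duration, and the rhythmic beat aims at the walking pattern. The T0 week has no such programme. If the T1 week does, the change from T0 to T1 contains two interventions.

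This matters most for the pooled analyses. Section 6.ii says that the main aim is mechanistic and rests on pooled data, with no placebo arm. An effect shared by both arms cancels in a comparison between arms, but not in a change from baseline. Extra walking prompted by the app could then be read as carry-over of treadmill gains into daily life. Four sites could also settle the order differently, each in line with the protocol.

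A second problem compounds this. The only daily-life time point named in the randomised comparisons is the one that comes after the whole app period.

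**Working it through.** No sample-size figure enters this point. The check is of timing, then of what an app effect would do, then of the sections against each other.

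**1. The Post-Training phase.** Inputs from section 5.iv and section 5.ix.B: up to 2 days to the T1 functional assessment, up to 5 more days to the start of recording, and 7 days of recording. 2 + 5 + 7 = 14 days, which reproduces the stated length. The home week therefore fits inside the phase, and T2 is counted from its end.

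**2. Possible overlap.** Count days from the T1 functional visit. Recording runs from day *o* to day *o* + 7, with *o* between 0 and 5, so from days 0–7 at the earliest to days 5–12 at the latest. Let the app start on day *s*. The overlap is 7 − (*s* − *o*) days, limited to the range 0 to 7.
- App handed out at the T1 visit (*s* = 0): 7 of 7 days, or 100%.
- App handed out when recording ends (*s* = *o* + 7): 0 of 7 days, or 0%.

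The protocol permits both.

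**3. App access by T2.** If the phase takes its full 14 days, T2 falls between 14 + 7 × 10 = 84 and 14 + 7 × 14 = 112 days after the last session. App access is then 10 to 14 weeks if the app starts when the phase ends, and roughly 12 days longer if it starts at the T1 visit.

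**4. Effect on pooled change and on the contrast (illustration).** The protocol gives no figures here. Assume training effects of +300 (SDTT) and +600 (SDTT+) steps per day, and an app effect *a* that is equal in both arms.
- Pooled T2 − T0 = [(300 + *a*) + (600 + *a*)] / 2 = 450 + *a*. For *a* = 0, 500 and 1,000 this is 450, 950 and 1,450.
- Contrast between arms = (600 + *a*) − (300 + *a*) = 300 for every *a*.
- If the app worked differently in the SDTT+ arm by −200 to +200, the contrast would run from 100 to 500.
- At T1, if a fraction *f* of the week overlaps and the app acts at once, pooled T1 − T0 = 450 + *f* × *a*. This is 450 at *f* = 0, and 950 to 1,450 at *f* = 1 with *a* = 500 to 1,000.

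**5. Effect on the association and mediation models.** A uniform app effect goes into the intercept, and the planned multilevel model can absorb a shift common to one site. Slopes and the mediated path are distorted only if app uptake varies between patients in step with laboratory gain or mGES. The app is optional and self-paced, so this is plausible, but it is an assumption.

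**6. When daily-life outcomes are recorded.**
- Section 5.i: before T0 and after T2; T1 is not named.
- Sections 5.xii.G and 6.ix: T0 and T1.
- Sections 5.vii.B, 5.ix.B and 5.xi.B, and the Figure 2 caption: T0, T1 and T2.
- Sections 6.vi and 6.vii: analysed under T2.

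On the section 5.xii.G schedule, the T2 data that 2a and 3a need are not collected. On the section 5.i schedule, the T1 data that the transfer analysis needs are not collected.

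**The case against.** The strongest reply is that the protocol already implies the clean order. The T1 home assessment is part of the Post-Training phase, the maintenance period is the next section, and T2 is timed from the end of Post-Training. Figure 2, which is not visible in the text at hand, may show the sequence. This reading is reasonable, and under it the T1 week is free of the app. A reader might infer that transfer of treadmill training cannot be isolated at all; the documents do not support that. They leave the order open, and no sentence requires either one.

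A second reply is that both arms are offered the same programme. This stands for the randomised contrast, and the Trial Summary describes the sequence openly. It does not help the pooled change from baseline.

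A third reply is that T1 is partly covered. The description of work package 3 (section 5.ii.C) plans a recording week at each time point with repeated-measures models, 3a uses time (T0, T1, T2) by group, and a diary logs physical activity in the T1 week to support comparability with T0. These soften the point, but the outcome lists in 2a and 3a still place daily-life measures only under T2. How diary and calendar data enter the models may be left to a statistical analysis plan. A diary can show overlap but cannot undo it.

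Finally, the T2-minus-T0 outcomes in 3b are laboratory measures, and the transfer and mediation analyses use T1 minus T0 only. It would be wrong to say that T2-minus-T0 daily-life change is planned as the measure of transfer.

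**Conclusion.** The point holds as a gap in the schedule and a conflict between sections. The share of the T1 home week inside the app programme can be anywhere from 0% to 100%, and the pooled transfer and mediation analyses have no app-free control to separate the two. The size of any distortion cannot be derived from the protocol. The step counts above are assumptions, and distortion of slopes also needs uptake to vary with laboratory gain or self-efficacy.

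The randomised contrast at T2 is not confounded, although a reader might infer that it is. It estimates SDTT+ followed by the home programme against SDTT followed by the same programme, and changes only if the app works differently by arm. What T2 cannot show is treadmill training alone: since no group goes without the app, pooled T2-minus-T0 change and retention cannot be attributed to treadmill training by itself. Settling the order and time points is worthwhile because a T1 week recorded during the programme cannot be recovered later.

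**What to change.** 1. State that the T1 home week is completed before the goal-setting session and app hand-out, within the existing 14-day Post-Training phase. This is one sentence. The cost is that the app starts up to about 12 days (5 + 7) after the T1 visit; T2 timing is unchanged.
2. Reconcile the home-recording time points in sections 5.i, 5.iv (with the Figure 2 caption), 5.xi.B, 5.xii.G and 6.ix, and add T1 daily-life outcomes to the SDTT+ versus SDTT comparison in 2a and 3a. Sections 5.xii.G and 6.ix already plan the T1 recording, so no new data are needed.
3. Describe T2 and T2-minus-T0 results, including what section 6.x calls retention, as the result of training plus home programme. This is wording only.
4. Do not add app adherence from the weekly calendars as an adjustment covariate in the T2-minus-T0 models. It arises after randomisation and may lie on the pathway under study. If it is used, label the analysis exploratory.
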